#### Analysis of secondary outcomes

For each of the continuous secondary outcomes (DRI, EQ-5D-5 L, and POSAS) the mean and standard deviation for each intervention arm will be reported. Assuming approximate normality is established, multi-level mixed-effects linear regression models, using repeated measures (level 1) nested within participants (level 2), will be used. The suitability of the assumption of approximate normality will be explored by plotting the residuals from this model. The model will include a random effect to account for any heterogeneity in response due to recruitment centre (level 3). The model will also include fixed effects to adjust for open versus closed fractures, ISS level (≤ 15 vs ≥ 16), participant age and participant gender, and, where appropriate, pre-injury values (DRI and EQ-5D-5 L). Trends over time in each intervention arm will be examined by plotting these, and, if trends differ between arms, interactions between treatment and time will be included in the model. The adjusted difference between the treatment arms at each time point will be reported. This analysis will be conducted for the ITT population using the available case dataset. The analysis of the DRI will be repeated using an imputed dataset. Data will be imputed using MI under the MAR assumption.

If, for any of these variables, approximate normality is not appropriate, the first approach will be to consider a transformation of the data or the use of a different metric such as change from baseline to attain normality. If normality cannot be achieved by transformation, the data will be analysed using a non-parametric equivalent (Mann-Whitney U-test) with no adjustment and medians and interquartile ranges will be reported for each treatment arm.

In addition, supplementary analyses of the DRI and EQ-5D utility variables will be conducted using area under the curve (AUC) summary statistics [27]. For each intervention arm, a linear combination of the parameter estimates at each time point (baseline to 6 months) from the mixed effects models will be used to calculate the AUC, thus providing an overall estimate of recovery over time for each intervention arm. This analysis will be conducted for the ITT population using the available cases dataset. The difference between the two groups will be calculated and compared using a *t*-test.

The DN4 will be analysed using similar methods to those outlined for the primary outcome. The number and proportion of individuals deemed to have neuropathic pain (DN4 ≥ 3) will be reported for each treatment arm. A multi-level mixed-effects logistic regression model with repeated measures (level 1) nested within participants (level 2) will be used. The model will be adjusted for recruitment centre as a random effect (level 3), and fixed effects will be included to adjust for open versus closed fractures, ISS level (≤ 15 vs ≥ 16), participant age, and participant gender. Trends over time will be examined, and, if appropriate, interactions between treatment and time will be included. Results will be presented as ORs with associated confidence intervals. The unadjusted OR and associated 95% confidence interval will also be reported. This analysis will be conducted for the ITT population using the available case dataset.

Similar methods will also be used to analyse complications. The number and percentage of people experiencing each complication in each treatment arm will be reported. If there are sufficient numbers of events, a mixed-effects logistic regression model will be used to compare the rates of complications between intervention arms. The model will include a random effect for recruitment centre and fixed effects for open versus closed fractures, ISS level (≤ 15 vs ≥ 16), participant age, and participant gender. If there are not sufficient numbers of events to fit an adjusted model, unadjusted differences between intervention arms will be calculated using a chi-squared test. This analysis will be conducted for the ITT population using the available case dataset. Temporal patterns of complications will be presented graphically and, if appropriate, a time-to-event analysis (Kaplan-Meier survival analysis) will be used to assess the overall risk and risk within individual classes of complications.

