#### Secondary outcomes

The secondary outcome measures, recorded at 3 and 6 months post-injury unless otherwise stated, are as follows:Disability Rating Index (DRI) [18]: a self-administered, 12-item visual analogue scale (VAS). Each item is scored from 0 (carry out task without difficulty) to 100 (not at all). Total scores are calculated as an average across all 12 items with higher scores indicating greater disability.Euroqol EQ-5D-5 L [19, 20]: a self-reported outcome measure consisting of five dimensions each with five possible responses which are converted to multi-attribute utility scores where 1 represents perfect health, 0 represents death, and scores less than 0 are possible. The EQ-5D-5 L also includes a 0–100 VAS recording overall health status with higher scores representing better health.Doleur Neuropathique Questionnaire (DN4) [21]: seven yes/no questions with total scores being the number of questions answered yes. Scores of 3 or greater are considered indicative of neuropathic pain.Patient-reported scar assessment using the patient scale from the Patient and Observer Scar Assessment Scale (POSAS) [22]: six questions each scored out of 10. The answers are summed to give an overall score out of 60 with higher scores indicating better healing. This scale is also measured at 30 days post-injury.Complications grouped into three categories: (i) local complications related to the injury or operation—this will include wound healing assessment at 30 days using photographs, signs of infection up to 6 months, and other local complications; (ii) systemic complications related to the injury or operation—this will include other related SAEs; and (iii) unrelated SAEs.

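### For the continuous secondary outcomes, plotted trends decide whether treatment-by-time is fitted, so the promised differences at each time point may be one common estimate reported at every visit

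*SAP article*

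**What the plan says.** All of this is in the SAP article, mainly under Analysis of secondary outcomes.

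- **Choice of model.** DRI, EQ-5D-5L and POSAS are analysed with multi-level linear models. On trends, the article says "Trends over time in each intervention arm will be examined by plotting these", and then "if trends differ between arms, interactions between treatment and time will be included in the model". It names no test, threshold or assessor.
- **What is reported.** The next sentence has no condition attached: "The adjusted difference between the treatment arms at each time point will be reported".
- **AUC for DRI and EQ-5D utility.** Each arm's AUC is to be "a linear combination of the parameter estimates at each time point (baseline to 6 months) from the mixed effects models". The two arms are then compared with a t-test.
- **Baseline.** The same models adjust for "where appropriate, pre-injury values (DRI and EQ-5D-5 L".
- **DN4.** The wording is looser still: "Trends over time will be examined, and, if appropriate, interactions between treatment and time will be included".
- **Timing of measurements.** Under Secondary outcomes: "The secondary outcome measures, recorded at 3 and 6 months post-injury unless otherwise stated". POSAS is also measured at 30 days.

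**The concern.** The rule for choosing the model and the promise about reporting do not fit together. The promise needs a model with a separate treatment effect at each visit, and the rule supplies that model only when someone judges that the plots differ. Observed trends always differ somewhat, so without a criterion the rule does not fix the model. The choice is made after seeing outcomes by arm, in an article whose Discussion says that it exists to limit data-driven results.

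The Objectives section places the secondary comparisons at 3 and 6 months. If the interaction is left out, a reader will see a difference listed at each visit and take these as separate estimates, when their equality was imposed. The AUC would look like a further analysis but would repeat the main-effect test.

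A smaller gap concerns baseline. The AUC is to use model estimates from baseline onward, while pre-injury DRI and EQ-5D enter as covariates. As described, the model then has no baseline time-point parameter to feed into the AUC.

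**Working it through.** The article gives no figure on this point, so there is none to reproduce. The check is algebra followed by an illustration on stated assumptions. I take time main effects to be fitted, although time is not named among the fixed effects.

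**1. What the model without interaction estimates.** Let d3 and d6 be the true arm differences at 3 and 6 months. With balanced data, the single treatment coefficient targets d = (d3 + d6)/2. It is reported at both visits with the same interval.

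**2. What happens to the AUC.** Apply the trapezoid rule at 0, 3 and 6 months, with zero arm difference at baseline:

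(3/2)(0 + d3) + (3/2)(d3 + d6) = 3·d3 + 1.5·d6.

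With one common effect this becomes 3d + 1.5d = 4.5·d. If the shift is taken as constant from month 0, it is 6·d. Either way it is a constant times d, so its test is the main-effect test again.

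Example, d3 = 4 and d6 = 2: the target is 3×4 + 1.5×2 = 15 point-months. The common-effect model gives d = 3 at both visits and 4.5×3 = 13.5.

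**3. How often the choice matters.** The following are assumptions, not in the article:

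- 616 per arm (770 × 0.8, borrowing the 20% loss allowance from Sample size).
- SD 25 at each visit.
- Within-person correlation ρ of 0.5 or 0.7.
- A two-sided 5% interaction test standing in for the visual judgement.

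Standard errors, with v = 2×25²/616 = 2.03:

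- One time point: √v = 1.42.
- Common effect: √(v(1+ρ)/2) = 1.23 (ρ = 0.5) or 1.31 (ρ = 0.7).
- Interaction, d6 − d3: √(2v(1−ρ)) = 1.42 or 1.10.

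Pairs of estimated differences were simulated 200,000 times. The separate estimates were used when the interaction test was significant, and the common effect otherwise.

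| True d3, d6 | ρ | Interaction enters | 6-month coverage under the rule | 6-month coverage if the common effect is always used |
|---|---|---|---|---|
| 4, 2 | 0.5 | 28.8% | 88.9% | 87.2% |
| 4, 2 | 0.7 | 44.0% | 91.2% | 88.2% |
| 4, 0 | 0.5 | 80.3% | 89.5% | 63.4% |
| 4, 0 | 0.7 | 95.1% | 93.9% | 66.8% |
| 3, 3 | 0.5 | 5.0% | 94.3% | 95.0% |
| 3, 3 | 0.7 | 5.0% | 94.6% | 95.0% |

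The loss of coverage comes from changes too modest to trigger the interaction reliably. When the effect is constant, almost nothing is lost.

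**4. Price of always fitting the interaction.** The ratio of standard errors, one time point to common effect, is √(2/(1+ρ)): 1.15 at ρ = 0.5 and 1.08 at ρ = 0.7. Time-specific intervals are therefore about 8% to 15% wider than the common-effect interval.

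**The case against.** The best defence is that the rule catches the cases that matter. A change of 6 points between visits (8 then 2, say) is 6/1.42 = 4.2 standard errors at ρ = 0.5, so the interaction would enter about 99% of the time, and over 99.9% at ρ = 0.7. That stands: large changes would seldom be averaged away, and the exposure is to modest ones. It is also true that under General analysis principles no trial conclusion rests on secondary outcomes, and that the AUC analyses are labelled supplementary.

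A reader might infer more than the article supports:

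- **That the time-specific differences and the AUC cannot be obtained at all without the interaction.** They can. The differences come out forced equal and, with time main effects, the arm profiles forced parallel. What is lost is separate estimation.
- **That the t-test between model-derived AUCs is undefined.** An estimated difference divided by its standard error and referred to a t distribution is a proper test. At this sample size it agrees with a Wald test.
- **That DN4 has the same contradiction.** The article promises odds ratios for DN4, not an effect at each time point. Only the discretionary rule is at issue there.
- **That the plots will be seen with the allocation revealed.** They are by arm, so the choice is data-driven, but the article does not say whether the arms will be labelled.
- **That baseline is certainly only a covariate.** Adjustment is where appropriate, and the article does not say that the baseline and pre-injury values are the same measurement. The gap is one of definition, and the AUC difference is computable once a baseline convention is stated.

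**Conclusion.** The point holds in limited form. For DRI, EQ-5D-5L and POSAS, the article promises time-specific differences unconditionally but fits the model that estimates them only after an uncriterioned look at outcome plots. Without the interaction, the reported differences are one coefficient with one interval, and the AUC difference is a fixed multiple of it.

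The size is moderate. For a true effect falling from 4 to 2 points, the pooled estimate is off by 1 point at each visit, and nominal 95% intervals at 6 months cover 89% to 91%. These figures depend on the assumed SD, numbers, correlation and 5% stand-in test, and show direction and rough size only. An informal visual judgement could do better or worse. The primary analysis is not touched.

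**What to change.** - **Continuous outcomes.** Prespecify categorical time and treatment-by-time for DRI, EQ-5D-5L and POSAS whatever the plots show. Report the difference at each time point from that model. If a pooled effect is wanted, give it as a contrast of the same model. The plots can stay as description.
- **DN4.** Replace the discretionary wording with the same prespecified terms.
- **AUC.** Keep the pre-injury value as a covariate. Define the DRI and EQ-5D AUC difference as the contrast 3·d3 + 1.5·d6 (time in months, zero arm difference at baseline), with its standard error from the model covariance matrix.

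The cost is a change of wording and one extra parameter where there are two follow-up times, or two for POSAS with three, in a trial that recruited 1548. Time-specific intervals will be somewhat wider than a common-effect interval (about 8% to 15% on the assumptions above). Under Trial status, analysis follows the end of follow-up, so the wording can be settled before then.

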### Statistical analysis

#### General analysis principles

Two analysis populations will be considered, the intent-to-treat (ITT) population and the per-protocol (PP) population. The ITT population will include all participants randomised with the exception of those who: (i) prospectively declined consent but were subsequently randomised in error; (ii) retrospectively declined consent and requested that all their data were removed; or (iii) withdrew and requested that all their data were removed. Participants will be analysed according to the group to which they were randomised. The PP population will be analysed according to the treatment they actually received. Participants with major protocol deviations or violations will be excluded from the PP population. Major protocol deviations are those who did not satisfy the eligibility criteria (for example their wound could not be closed primarily), those who did not receive the allocated treatment, and those for whom insufficient data are available on the primary outcome. The definition of the PP population will be finalised during a blinded analysis of the data prior to the primary analysis time point.

A significance level of 0.05 will be used throughout, and 95% confidence intervals will be reported. The primary conclusion of the trial will be based on the results from the primary analysis of the primary outcome. Sensitivity analyses of the primary outcome will be performed to assess whether these results are robust. All analyses of secondary outcomes will be considered as supporting the primary analysis, and conclusions of the trial will not be based on these outcomes.

All analyses will be carried out using appropriate, validated statistical software such as STATA [24] or R [25]. The relevant package and version number used for the analysis will be recorded and reported.

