#### Compliance

The randomised intervention in this trial is the dressing (standard or NPWT) applied to the closed fracture wound at the end of surgery. This intervention occurs at a single time point, and compliance is therefore defined as the proportion of participants in each arm receiving the treatment to which they were randomised. The number (and percentage) of participants receiving the assigned dressing and receiving another dressing or no dressing in each arm will be summarised as well as the reasons for not receiving the randomised treatment. Details of what was provided instead will also be summarised.

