#### Analysis of primary outcome

The numbers and percentages of ‘deep infections’ occurring up to 30 days post-randomisation in the two study intervention groups, NPWT and standard dressing, will be calculated. The rates of deep infection in the two study groups will be compared using a mixed effects logistic regression model. The model will include a random effect to account for any heterogeneity in the response due to recruitment centre. Fixed effects to adjust for open versus closed fractures, ISS level (≤ 15 vs ≥ 16), participant age, and participant gender will also be included. Participant age and gender are included in the model since there is evidence that older men have worse outcomes after major trauma. The result will be reported as an odds ratio (OR) with associated 95% confidence interval and *p* value for comparison between the two treatment groups. The unadjusted OR and associated 95% confidence interval will also be reported.

This analysis will be conducted for the ITT population using the available case dataset. As sensitivity analyses, the analysis will be repeated for: (i) the ITT population using an imputed dataset (best case worst case analysis); and (ii) the PP population using the available case dataset. In addition, a sensitivity analysis taking account of the competing risk of death [26] will be conducted if a sufficient number of deaths have occurred prior to 30 days, that is if more than 5% of participants have died prior to this time point.

If a significant treatment effect of NPWT is identified in the primary analysis, an exploratory subgroup analysis will be conducted to investigate whether this effect is moderated by the underlying risk level of the wound. This will be done by repeating the primary analysis and including wound location (above or below the knee) as a covariate. Wound location will be used as a proxy for wound risk level due to differences in soft-tissue cover; there being less soft-tissue cover below the knee.

The main analysis of the primary outcome (ITT population using the available case dataset) will be repeated using the alternative definition of ‘deep infection’, including infections occurring up to 90 days after injury. If any of the sensitivity analyses conducted for the primary endpoint (30 days) demonstrated substantially different results from the primary analysis, these analyses will be repeated for the rates of deep infection up to 90 days.

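### Complications and SAEs are analysed only by randomised arm, so an excess of dressing-related harm may be diluted by switching, by an unknown and possibly small amount

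*SAP article*

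**What the plan says.** - **What counts as a complication.** The Secondary outcomes section groups complications into local ones, systemic ones and unrelated events. SAEs fall under this outcome: for the systemic group "this will include other related SAEs; and (iii) unrelated SAEs" form the last part of the list.
- **How complications are tabulated.** Analysis of secondary outcomes states: "The number and percentage of people experiencing each complication in each treatment arm will be reported". A mixed-effects logistic model follows if events are numerous enough, otherwise a chi-squared test.
- **In which population.** The same section says: "This analysis will be conducted for the ITT population using the available case dataset. Temporal patterns of complications will be presented graphically". No second population is named.
- **How ITT groups people.** General analysis principles: "Participants will be analysed according to the group to which they were randomised".
- **Non-receipt is expected.** Under Compliance, the numbers "receiving the assigned dressing and receiving another dressing or no dressing in each arm will be summarised", together with reasons and details of what was given instead.
- **The per-protocol (PP) set.** General analysis principles says "The PP population will be analysed according to the treatment they actually received", but the same paragraph excludes anyone who did not receive the allocated treatment. Its use is set under Analysis of primary outcome, as sensitivity analysis "ii) the PP population using the available case dataset". That covers deep infection at 30 days and, conditionally, up to 90 days.

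**The concern.** A local complication caused by one dressing in a participant randomised to the other is counted under the arm of the dressing that was not on the wound. For the superiority question on deep infection, the resulting shrinkage towards no difference is conservative. For harm caused by a dressing it is not, because a real excess looks smaller. The plan gives the primary outcome a check against non-receipt (the PP analysis) and gives harms none, although the Compliance data would allow one. At stake is whether a finding of little or no excess harm could partly reflect switching, with nothing in the planned output to show it.

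**Working it through.** **1. The plan's own figure.** Sample size inputs: 15% v 9%, two-sided 5%, 90% power. The two-proportion normal approximation without continuity correction gives 615 per group (power at 615 is 90.0%), as the plan states. Allowing for 20% loss, 615/0.8 = 769 per arm, 1538 in total, against the stated 770 and 1540. These figures are not in dispute. The same method is used below.

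**2. Dilution formula.** Let p1 and p0 be the complication risks with NPWT and with the standard dressing. Let c1 be the share of the NPWT arm given the standard dressing, and c0 the share of the standard arm given NPWT. If switchers have the same underlying risk as everyone else:

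- NPWT arm: p1(1 - c1) + p0·c1
- standard arm: p0(1 - c0) + p1·c0
- ITT difference: (1 - c1 - c0)(p1 - p0)

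The retained share, 1 - c1 - c0, does not depend on the risks.

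**3. Numbers.** The article gives no complication rate and no switching rate, so p0, p1, c1 and c0 are all assumptions. Recruitment was 1548 (Trial status); with 1:1 allocation an even split gives 1548/2 = 774 per arm, here taken as fully followed up.

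| c1, c0 | Retained | 5% v 2%: points; OR; power | 10% v 5%: points; OR; power |
|---|---|---|---|
| 0, 0 | 100% | 3.00; 2.58; 89.5% | 5.00; 2.11; 96.3% |
| 2%, 2% | 96% | 2.88; 2.47; 87.0% | 4.80; 2.04; 94.9% |
| 5%, 0 | 95% | 2.85; 2.50; 87.0% | 4.75; 2.05; 94.8% |
| 5%, 5% | 90% | 2.70; 2.32; 82.5% | 4.50; 1.95; 92.0% |
| 10%, 10% | 80% | 2.40; 2.09; 72.9% | 4.00; 1.80; 84.9% |
| 20%, 5% | 75% | 2.25; 2.09; 70.1% | 3.75; 1.78; 81.9% |

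Rare or one-way switching costs little. The loss becomes material only at about 5% each way or more. For participants given some other dressing or none, the formula does not apply and the direction depends on their own risk.

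**4. Could the PP set serve instead?** No. It is not applied to complications, and as defined it drops the participants whose dressing differed from their allocation, so it cannot show their harm under the dressing they had.

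**5. How far can a comparison by dressing received be trusted?** Suppose there is no true effect, the overall risk is 3%, and 10% of the NPWT arm are given the standard dressing because their wounds carry three times the risk of the rest (all assumed). Then 0.9r + 0.1(3r) = 3% gives r = 2.5%, and 7.5% in the switchers. By dressing received, NPWT has 2.5% and standard has (3% + 0.1 × 7.5%)/1.1 = 3.4%, an OR of about 0.73 from selection alone. With 5% switching and twice the risk, r = 3%/1.05 = 2.86%, standard has (3% + 0.05 × 5.71%)/1.05 = 3.13%, and the OR is about 0.91.

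**The case against.** The strongest reply is that nothing here is misstated. ITT is a sound randomised comparison, it is named and defined, and a further supportive table might be called a matter of taste. Several parts of the reply stand.

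- **Scope.** A reader might infer that ITT makes NPWT look too safe on every complication and SAE. The article does not support that. Local complications include wound healing and signs of infection, which NPWT is hoped to improve; there dilution is conservative. For unrelated SAEs no dressing effect is expected.
- **Size.** A reader might also infer that dilution is established. It is not: no switching rate is given, and nothing indicates that the standard arm commonly receives NPWT.
- **Confounding.** Switching may depend on the wound. General analysis principles itself gives a wound that could not be closed primarily as an example of a deviation. Step 5 shows that grouping by dressing received can mislead in the very direction feared, so it cannot replace ITT.
- **Consequence.** Non-receipt will be reported by arm, which lets a reader gauge possible dilution, and the trial's conclusions are not to rest on secondary outcomes.
- **Condensed article.** Routine safety listings may sit in a fuller document. The population for the complications analysis, however, is stated here, so that choice can be reviewed.

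What the reply leaves unanswered is that the dressing received is recorded, expected to differ from allocation in some participants, and never set against their complications.

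**Conclusion.** The concern holds in limited form. As the article stands, complications and SAEs are compared by randomised arm only, and an excess of dressing-related harm may be diluted if participants switch. The share of the difference retained is 96%, 90% and 80% at 2%, 5% and 10% switching each way. In the assumed 5% v 2% case, power falls from 89.5% to 87.0%, 82.5% and 72.9%. All of this rests on assumed rates, on switching between the two dressings, on switchers having the same underlying risk as others, and on complete follow-up of 774 per arm. The true effect may be small. The ITT analysis is not invalid and should remain the main one; what is missing is a cheap supportive view of harm.

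**What to change.** In Analysis of secondary outcomes, after the sentence fixing the ITT population for complications, add wording such as:

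> *As a supportive analysis, the number and percentage of participants with local complications and with related SAEs will be tabulated by the dressing actually applied at the end of surgery (NPWT; standard; other or none), also showing the randomised arm. This comparison is not randomised and may be confounded by wound condition in either direction; it will be read beside the ITT result and not in place of it.*

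Extending the PP set as now defined would not do the job.

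The cost is a short addition to the plan and one table from data that the Compliance section already calls for. The real downside is the risk of over-reading a confounded comparison, which the label and the display by randomised arm are meant to limit. According to Trial status, follow-up was still running and the analysis was to come afterwards, so at that point the table could still be prespecified. If it is added after results are seen, it should be reported as post hoc.

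### The optional Kaplan-Meier analysis of complications makes no provision for deaths and, run in the standard way, would slightly overstate complication risk

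*SAP article*

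**What the plan says.** In the SAP article, under Analysis of secondary outcomes, complications are first reported as numbers and percentages by arm. If events are sufficient, "a mixed-effects logistic regression model will be used to compare the rates of complications between intervention arms"; if not, a chi-squared test is used. After a graphical display of timing, the section adds, on the condition that this is appropriate: "a time-to-event analysis (Kaplan-Meier survival analysis) will be used to assess the overall risk and risk within individual classes of complications". No other time-to-event method is named for complications, and the section does not say how a death is handled.

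Under Secondary outcomes, complications fall into three classes: local, systemic (including other related SAEs) and unrelated SAEs. The local class includes "signs of infection up to 6 months, and other local complications".

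Under Analysis of primary outcome, the plan provides "a sensitivity analysis taking account of the competing risk of death" for deep infection at 30 days, with the condition "if more than 5% of participants have died prior to this time point". Under Loss to follow-up, withdrawals, and missing data, deaths and their causes are to be reported separately, with no link to the analysis of complications.

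**The concern.** A participant who dies can no longer develop a wound complication. When Kaplan-Meier is applied to a non-fatal event, a death is ordinarily treated as censoring, as though the participant remained at risk and were merely unobserved. One minus Kaplan-Meier then exceeds the proportion who actually have the complication whenever some participants die before having one. The direction follows from the estimator and needs no assumed rate; only the size does.

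The plan accepts the principle elsewhere. It foresees that deaths within 30 days might distort the primary result and sets a threshold for dealing with them. Cumulative deaths at 6 months cannot be fewer than at 30 days, yet the complication curves have no provision, not even a conditional one. At stake is the accuracy of the absolute risks read from those curves, chiefly for local complications, the class closest to the dressing question.

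**Working it through.** The plan gives no figure on this point to reproduce, so the check is the size of the overstatement.

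**Inputs.** Follow-up of complications to 6 months (Secondary outcomes). Mortality is not given, so it is assumed over a range. The nearest figure, under Sample size, is up to 20% of primary outcome data lost, but that pools death with loss to follow-up. The 5% trigger equals 0.05 × 1548 = 77.4, so 78 or more deaths among the 1548 recruited.

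**From the Kaplan-Meier value to the true incidence.** Take constant cause-specific hazards over 6 months. Let p be the value of one minus Kaplan-Meier and m the mortality.

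- Hazards: hc = −ln(1 − p), hd = −ln(1 − m)
- True cumulative incidence: hc/(hc + hd) × [1 − exp(−(hc + hd))]

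For p = 20% and m = 5%: hc = 0.2231 and hd = 0.0513, total 0.2744. The incidence is 0.2231/0.2744 × (1 − 0.76) = 0.813 × 0.24 = 19.5%.

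For p = 20% and m = 10%: hd = 0.1054, total 0.3285. The incidence is 0.679 × 0.28 = 19.0%.

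For p = 30%, the same steps give 29.3% and 28.6%.

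**From the true incidence to the Kaplan-Meier value.** Let c be the true incidence of the complication and d the incidence of death before it. With L = −ln(1 − c − d), one minus Kaplan-Meier is 1 − exp(−L × c/(c + d)). For c = 15% and d = 5%: L = 0.2231, times 0.75 = 0.1674, giving 15.4%.

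| True incidence | d = 1% | d = 2% | d = 5% | d = 10% | d = 20% |
|---|---|---|---|---|---|
| 5% | 5.03% | 5.05% | 5.13% | 5.27% | 5.59% |
| 15% | 15.1% | 15.2% | 15.4% | 15.9% | 16.9% |

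The relative overstatement is about 0.5%, 1%, 2.7%, 5.6% and 12%. The last column is an extreme value, because the 20% in the plan is not mortality alone.

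**If every death came before every complication.** The Kaplan-Meier value is c/(1 − d). At c = 15% and d = 5% it is 0.15/0.95 = 15.8%.

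**Difference between arms with equal mortality.** Using 15% and 9% (the plan's infection rates, for illustration only), a true difference of 6.0 points becomes 15.41 − 9.24 = 6.17 at d = 5%, and 6.35 at d = 10%.

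**The case against.** The case against is strong on weight. The Kaplan-Meier analysis is conditional and supplements a graph. Complications are compared by percentages and logistic regression, or chi-squared, and none of these is touched. General analysis principles states that secondary outcomes only support the primary analysis. All of this stands and limits the point to a minor one. The condition does not remove it, however: it governs whether a time-to-event analysis is run, and if one is run, Kaplan-Meier is the method named.

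It can also be said that censoring of deaths is inferred from the method and not stated. That is true. A fatal SAE might count as an event in the two classes that include SAEs, so death need not be purely a competing event there. It would still be one for local complications. Likewise, the word overall in that sentence most naturally means all classes pooled and does not promise a particular estimand. The point rests on the aim of assessing risk, not on that word.

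A reader might infer three stronger things that the document does not support:

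- **That the plan contradicts itself.** It does not treat death as a competing risk for the primary outcome in general. The primary analysis is a logistic model on available cases, and death enters only in a sensitivity analysis above a 5% trigger. Silence about an optional secondary analysis is a gap, not a contradiction.
- **That the arms would be biased unequally.** This needs mortality to differ by arm, and nothing in the document indicates that.
- **That disagreement with the crude percentages shows the fault.** With loss to follow-up, any estimator that adjusts for censoring, Aalen-Johansen included, can differ from crude percentages.

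**Conclusion.** The point holds as a minor one. If the optional analysis is run with deaths censored, it overstates the risk of non-fatal complications. On a true risk of 15% with 5% dying first, the excess is about 0.4 points under constant hazards, and 0.8 points if all deaths come first; at 1% mortality it is about 0.1 points under constant hazards. The direction requires only that some deaths precede complications and are censored. The size rests on assumed mortality and, except in the case where all deaths come first, on constant hazards. With equal mortality in both arms, the difference between arms hardly moves.

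**What to change.** In the sentence on time-to-event analysis of complications, replace Kaplan-Meier with cumulative incidence functions (Aalen-Johansen), with death as the competing event, overall and for each class. State that a fatal SAE counts as an event in any class whose definition includes it and as a competing event otherwise. The estimator also serves when deaths are few, since it then nearly coincides with one minus Kaplan-Meier, so no mortality trigger is needed. No between-arm test need be added: the plan assigns none to these curves, and the logistic model already compares the arms.

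The cost is about one line of SAP text and a standard routine in either software package the plan names. Sample size and the primary analysis do not change. Dates of death are needed, and a time-to-event analysis would need them in any case.
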